## 5. Calculations

The combination of OGTT and IVGTT will allow a comprehensive assessment of different aspects of beta cell function along with reliable measures of insulin sensitivity assessed during the euglycaemic clamp procedure [62]. Implementation of OGTT and isoglycaemic iv. glucose infusion will allow the quantification of the incretin effect based on established experimental model [63].

From OGTT data, following empirical indices of beta cell function will be derived: a) insulinogenic index (IGI) calculated as (30 min insulin – basal insulin)/(30min glucose – basal glucose); b) the early insulin response (EIR) calculated using formula (30 min insulin – basal insulin)/(30 min glucose)[64] or c) ratio of AUC for C-peptide divided by AUC for glucose (AUC_CP_/AUC_GLU_). AUCs are determined by trapezoidal method. Additionally, we intend to implement the established mathematical modelling from the OGTT to describe distinct features of beta cell function [62, 65-67]. The model describes the relationship between insulin secretion and glucose concentration coupled with a model of C-peptide kinetics. It provides not only basal insulin secretion rate and total insulin secretion during OGTT, but also three important indices of dynamic properties of beta cell function: beta cell sensitivity to glucose (glucose sensitivity), beta cell sensitivity to the rate of change of glucose (rate sensitivity) and a potentiation factor (representing relative potentiation of insulin secretion throughout the OGTT).

Based on IVGTT measurements, the incremental trapezoidal area of insulin and C-peptide during the first 10 min after glucose administration represents the first-phase insulin response or acute insulin response (AIR). AIR will be also measured as the sum of insulin and C-peptide concentrations during the first 10 min after the glucose challenge. The incremental insulin/C-peptide secretion during the last 50 min of IVGTT represents the second-phase insulin secretion. The C-peptide deconvolution will be applied to reconstruct insulin secretory rates independently of insulin clearance. It has also been proved that rate sensitivity derived from OGTT is correlated to AIR calculated from IVGTT and it is therefore a valuable marker of first phase insulin secretion [67].

The time profiles of hormones and incretins measured during OGTT and isoglycaemic i.v. glucose infusion will be expressed as AUCs. The incretin effect will be calculated as the ratio of oral to intravenous plasma insulin and C-peptide responses (as per original definition [63]). Additionally a mathematical model of beta cell function can be also employed to quantify the incretin effect on absolute insulin secretion and beta cell glucose sensitivity [3, 68].

Insulin sensitivity will be assessed as the mean glucose uptake, calculated from the glucose infusion rates during the last 60 min of euglycaemic clamp (M-value) and as the ratio of glucose infusion rates during the last 60 min of clamp and the mean steady state insulin levels during the same interval (M/I = S_I_ Index).

The disposition index (DI) as a measure of insulin secretion adjusted for insulin sensitivity will be calculated from the product of AIR and the M-value.

## 6. Statistical analysis

All data will be checked for distribution normality. In case of non-Gaussian distribution, log transformed data will be assured for further statistical evaluation.

1. Changes in beta cell function and other variables after gastric bypass surgery will be assessed by analysis of variance (ANOVA) with repeated measures. ANOVA models will include following factors:
   1. group factor as the between-subject factor (comparison between groups of bariatric patients with short- and long-standing T2DM and bariatric patients without T2DM)
   2. time factor (repeated measurements at baseline and two follow-up visits)
   3. treatment factor if appropriate - in case of repeated measurements within 1 follow-up (eg. GLP-1 profile during OGTT, basal + insulin-stimulated concentrations of adipokines and cytokines)

Time and treatment factors as the within-subject factors account for the repetition in the ANOVA model.

1. Relations between changes in beta cell function and clinical characteristics or changes in parameters of adipoinsular and enteroinsular axes will be evaluated using multivariate regression analyses.
2. For comparison of beta cell function and other variables after weight loss achieved following gastric bypass with results from BMI-matched non-bariatric controls, Mann-Whitney *U* test will be used.

Based of foregoing studies [10, 11, 19-21] a sample size of at least 15 subjects per subgroup can be safely expected to provide a sufficient statistical power to detect meaningful changes in beta cell function. Our sample size is based on feasible recruitment expectations at both sites: total number of 85 patients with an estimated drop-out rate of 10-12% during the follow-up, giving the final sample size of 75 patients – 50 patients with T2DM (among them approx. 40-50% with long-standing T2DM) and 25 patients without T2DM.

Nevertheless, based on published data [19] we have estimated mean values, variation and time-dependent covariance in individual groups for AIR (pmol/l) as a dependent variable characterizing the primary outcome. These data were used for power analysis for repeated measures ANOVA model consisting of Subject factor, Group as the between-subject factor and Time as the within-subject factor. For the statistical significance α=0.05 and power>0.8 (>80% chance to find significant relationships of factors and interaction with the dependent variable for all factors and interaction), at least 9 subjects per group should be included in the study. For the significance α=0.01 and power>0.8 for all factors and interaction, at least 13 subjects per group should be investigated. When considering power>0.95 we will need per group 13 subject for α=0.05 and 18 subjects for α=0.01. This means that 25 subjects per group will be fully sufficient for finding significant associations.

Moreover, a total number of 85 subjects will enable to perform reliable multivariate regression analyses in order to elucidate which factors, e.g. specific clinical characteristics or changes in gene expression, are most closely related to the improvement in beta cell function.

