# Specific Aims

## Zero hypothesis: There is no difference in terms of beta cell function in patients with short- and long-term history of T2DM following gastric bypass.

## Alternative hypothesis: There is a significant difference in terms of beta cell function in patients with short- and long-term history of T2DM following gastric bypass.

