**Primary objective**:

Comparison of the changes in beta cell function following gastric bypass in patients with short- and long-term history of T2DM

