**Primary outcome variable**:

Acute insulin response (AIR) to glucose during IVGTT will be used as a primary variable characterizing the beta cell function.

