# Novelty and importance of the proposed work

For the first time, our study will systematically evaluate beta cell function, by using three different glucose stimulation tests, in relation to adipoinsular and enteroinsular axes early and long-term after gastric bypass. Moreover, our study will also address the important question, if surgery induced beta cell function improvement also occurs after longer duration of T2DM when reduction of beta cell mass is expected. The parallel performance of an OGTT and an isoglycemic iv. glucose infusion will allow to quantify the incretin effects and thus, to precisely define the role of incretin hormones in the improvement of beta cell function after bariatric surgery. Our findings are therefore expected to bring new knowledge on possible reversibility of beta cell damage in long-standing T2DM.

Our approach of repeated biopsy at 1 year follow-up and comparison with control group matched for expected one-year postoperative BMI shall enable to identify surgery-specific changes in gene expression in adipose tissue independent on weight loss.

The sample size of this double-centre study which also includes controls will enable to achieve sufficient power of the study to reliably detect significant differences between groups as well as to perform valid multivariate regression analysis.

It is worth to point out that only the combined effort of our two study centres will let us achieve such a large sample size recruited in an acceptable period of time.

The results are expected to provide important new insight into the pathophysiology of disturbed beta cell function and its possible restoration in T2DM. Bariatric operations such as the gastric bypass procedure provide a unique model of rapid changes in pathological beta cell function and the results of this study on the long run may help to develop rational approaches to overcome beta cell failure in T2DM also with conservative means, e.g. by pharmacotherapy.

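### The stated ANOVA and its power statement do not single out the short- versus long-standing T2DM comparison of change in AIR, which is the primary question

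*Protocol*

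**What the plan says.** Under Specific Aims, the null hypothesis involves two groups: "There is no difference in terms of beta cell function in patients with short- and long-term history of T2DM following gastric bypass". The primary objective has the same two groups and speaks of change: "Comparison of the changes in beta cell function following gastric bypass in patients with short- and long-term history of T2DM". The primary variable is AIR: "Acute insulin response (AIR) to glucose during IVGTT will be used as a primary variable characterizing the beta cell function". Non-diabetic patients appear in none of these statements.

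Section 6 (Statistical analysis), item 1, gives one method for changes after bypass, a repeated-measures ANOVA. Its between-subject term is the "group factor as the between-subject factor (comparison between groups of bariatric patients with short- and long-standing T2DM and bariatric patients without T2DM"), and its within-subject term is the "time factor (repeated measurements at baseline and two follow-up visits").

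The power paragraph of the same section describes a "power analysis for repeated measures ANOVA model consisting of Subject factor, Group as the between-subject factor and Time as the within-subject factor" and promises a ">80% chance to find significant relationships of factors and interaction with the dependent variable for all factors and interaction". It gives 9, 13, 13 and 18 subjects per group for four combinations of alpha and power, and concludes that 25 per group is enough. The expected final sample is 75: 50 patients with T2DM, of whom 40-50% are long-standing, and 25 without.

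**The concern.** With three groups, the group test (2 df) and the group-by-time test (4 df) have as their null that all three groups are alike. Neither isolates short against long. If T2DM patients recover AIR and non-diabetic patients change little, the interaction can be significant although disease duration makes no difference. The protocol's own background makes such divergence plausible. It describes beta cell dynamics as preserved in obesity without diabetes, progressive loss in overt diabetes, and restoration of AIR in T2DM after biliopancreatic diversion.

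At stake is the trial's headline claim. A significant overall test could be read as an effect of diabetes duration when it only shows that diabetic and non-diabetic patients differ. The power statement has the same gap: high power for all factors and the interaction is not power for the comparison in the primary objective.

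**Working it through.** **1. How many groups the model has.** The group factor names three. The power text fits this, since 3 × 25 = 75 is the final sample and 50 T2DM patients split about evenly give 25 + 25, plus 25 non-diabetic. The drop-out arithmetic also agrees: 85 × 0.88 = 74.8 and 85 × 0.90 = 76.5.

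**2. The plan's own sample sizes.** The AIR means, SDs and covariances behind 9/13/13/18 are not printed, so these figures cannot be derived from the document. A noncentral-F check shows that one common effect size can produce all four numbers. This holds for a three-group group test and a three-group interaction, and equally for two-group versions of both. The figures are therefore coherent, but they do not reveal which comparison was powered.

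**3. How often the interaction rejects when short = long.** Assumptions: SD 1 at each visit on the analysis scale, equal correlation ρ = 0.5 between visits, two-sided α = 0.05. Completers: 55 × 0.88 ≈ 48 T2DM (28 short, 20 long; 20/48 = 42% long-standing) and 30 × 0.88 ≈ 26 non-diabetic. Both T2DM groups follow the profile 0, d/2, d over the three visits, and non-diabetic patients are flat.

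The noncentrality of the interaction is λ = [n_T n_N/(n_T + n_N)] × q d²/(1 − ρ), where q is the sum of squares of the centred unit profile.
- n_T n_N/(n_T + n_N) = 48 × 26/74 = 16.865
- q = (−½)² + 0² + (½)² = 0.5
- λ = 16.865 × 0.5 × d²/0.5 = 16.865 d², with 4 and 2 × (74 − 3) = 142 df

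| d (SD) | λ | P(reject), noncentral F | P(reject), simulation | Direct short-vs-long contrast |
|---|---|---|---|---|
| 0.5 | 4.22 | 33% | 34% | about 5% |
| 0.75 | 9.49 | 67% | 67% | about 5% |
| 1.0 | 16.86 | 92% | 92% | about 5% |

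Sensitivity to the assumptions:
- At ρ = 0.3 the same formula gives 24% / 51% / 79%. At ρ = 0.7 it gives 53% / 90% / 99%.
- If the full rise is present by the first follow-up (0, d, d; q = 2/3), simulation with 25/25/25 gives 43% / 87% / 98% for d = 0.5 / 0.8 / 1.0. With 30/20/25 it gives 43% / 86% / 97%. The direct test stays near 5% in both.

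**4. Does including non-diabetic patients cost power?** Take a true short-long difference of 0.9 SD and equal SDs in all groups. The T2DM-only contrast and the contrast using the pooled three-group error both have about 85-86% power, so the contrast loses nothing. The overall interaction depends on where non-diabetic patients lie. In one scenario it has 87-95%. In another (short rises 0.8 SD, long does not change, non-diabetic midway) it has 71-74% against 81-82% for the direct test. A large loss for the contrast appears only if the non-diabetic SD is 2 or 3 times that of T2DM patients. The pooled-error contrast then falls to about 59% or 23%.

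**5. What the primary contrast can detect.** For change in T2DM patients, 80% power, two-sided 0.05: (1.960 + 0.842) × √(1/n₁ + 1/n₂) in SDs of the AIR change.
- 25 vs 25: 2.802 × 0.2828 = 0.79
- 30 vs 20: 2.802 × 0.2887 = 0.81

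The SD of change is √(2(1 − ρ)) AIR SDs. In AIR SD units the detectable difference is thus 0.61-0.63 at ρ = 0.7, 0.79-0.81 at 0.5 and 0.94-0.96 at 0.3.

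**The case against.** The best defence is that no sentence says the primary hypothesis will be decided by the overall F test. Section 6 lists factors for models of beta cell function and other variables. Secondary objectives include patients without T2DM, so a non-diabetic level is legitimate. A short-versus-long contrast can be estimated inside a three-group model, and a separate analysis plan may name it. That stands against any claim that the trial will necessarily draw its conclusion from the wrong test. It does not remove the mismatch: the protocol itself fixes the group factor and rests its power on factors and interaction, so an added contrast would still leave the power statement aimed elsewhere.

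Four stronger readings are tempting, and the documents do not support them.
- **The group main effect would almost always be significant.** That needs a large baseline gap between non-diabetic and T2DM patients (1.5 to 2 SD in the runs made), which the protocol does not give. With non-diabetic patients flat at the level T2DM patients finally reach, it rejects in about 18-59% of trials for the gradual rise in step 3, and in about 10-29% for the early full rise.
- **Non-diabetic patients would swamp the comparison with extra variance.** No SDs are printed, and the planned log transformation of non-Gaussian data could reduce such a ratio.
- **The model cannot address "if surgery induced beta cell function improvement also occurs after longer duration of T2DM".** The change within the long-standing group is a simple time effect that can be estimated from the same cell means.
- **The hypothesis and the objective conflict.** The null hypothesis is loosely worded, but the primary objective directly after it says change, and item 1 of section 6 analyses changes with baseline included.

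**Conclusion.** The point holds in this form: the primary objective compares AIR change between two T2DM groups, while the stated model adds a non-diabetic level and the stated power covers its factors and interaction without naming the short-versus-long contrast. That an overall test can reject with short = long follows from its null hypothesis and needs no assumed numbers. The illustrative 34% / 67% / 92% against about 5% rests on the assumed SDs, correlation, recovery profile and flat non-diabetic course; other choices move the rates, not the direction. A material loss of power for the contrast is not shown. The three-level reading rests on the wording of the group factor, supported by 3 × 25 = 75.

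**What to change.** - Name one primary test: the short-minus-long difference in change of AIR from baseline to a pre-stated follow-up visit, with 95% CI. Either a contrast within the three-group model with group-specific variances, or an analysis of T2DM patients only, would do.
- Make the overall group and group-by-time tests, and all comparisons with non-diabetic patients, secondary.
- Word the null hypothesis as no difference in change.
- Restate power for this contrast with the expected 25-30 short and 20-25 long completers: about 0.8 SD of the AIR change at 80% power. Print the assumed AIR means, SDs and correlations.

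The cost is wording in Specific Aims and section 6 and one power recalculation. No further patients, visits or measurements are needed.

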## 2. Background and current status of research in the proposed field of the study

Epidemiological evidence confirms that weight loss significantly decreases the risk for development of type 2 diabetes [1]. Morbid obesity per se is associated with profound insulin resistance and subsequent hypersecretion of insulin but the dynamics of beta cell function are still preserved [2]. On the other hand, overt diabetes is characterized by a progressive loss of beta cell glucose sensitivity [3]. In contrast to traditional weight reduction treatments, bariatric surgery has been proven not only to induce a sustained long-term weight loss but also to resolve type 2 diabetes in the majority of patients and it therefore represents an interesting model of weight loss and related changes in glucose metabolism [4]. However, resolution rates of diabetes after bariatric surgery clearly depend on the specific type of operation rather than on the amount of weight loss per se [5]. Bilio-pancreatic diversion (BPD) has consistently been found to show the highest remission rate (i.e. about 99%) followed by Roux-en-Y gastric bypass (85%), whereas purely restrictive procedures such as gastroplasty and gastric banding induce lower rates of diabetes resolution (72% and 48%; respectively). Together these findings point to distinct influences of different surgical procedures on glucose metabolism with those excluding the duodenum from the passage and enhancing the delivery of nutrients to the hindgut being the most effective.

Remarkably, in many cases the beneficial effect of bariatric surgery on glucose metabolism occurs within days after surgery, i.e. even before a significant weight loss has been achieved. However, in other cases glucose metabolism only gradually improved in parallel with the progression of weight loss until a complete remission has been achieved [6-8]. Observational clinical studies suggest that the chance of recovery from T2DM due to surgery decreases with increasing duration of the disease [9]. Though, surgery-induced remission of T2DM is also not uncommon in patients with long standing diabetes. Thus, strong predictors for the course of T2DM after gastric bypass surgery are still lacking which may result from insufficient preoperative metabolic characterisation of T2DM patients in many foregoing observational studies.

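### The primary question compares short- with long-standing T2DM, but the stated ANOVA has a three-level Group factor that includes non-diabetic patients, so its Group tests do not match the primary null

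*Protocol*

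**What the plan says.** Under Specific Aims, the Protocol's null hypothesis reads "There is no difference in terms of beta cell function in patients with short- and long-term history of T2DM following gastric bypass". The primary objective is "Comparison of the changes in beta cell function following gastric bypass in patients with short- and long-term history of T2DM", and the primary variable is AIR: "Acute insulin response (AIR) to glucose during IVGTT will be used as a primary variable characterizing the beta cell function". All of this concerns two groups of diabetic patients.

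Methodology section 6, item 1, assigns changes in beta cell function and other variables to a repeated-measures ANOVA. Its between-subject term is the "group factor as the between-subject factor (comparison between groups of bariatric patients with short- and long-standing T2DM and bariatric patients without T2DM", and its within-subject term is the "time factor (repeated measurements at baseline and two follow-up visits". That makes three groups by three visits.

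The power paragraph of the same section describes a "repeated measures ANOVA model consisting of Subject factor, Group as the between-subject factor and Time as the within-subject factor" and claims a more than 80% "chance to find significant relationships of factors and interaction with the dependent variable for all factors and interaction". It does not say how many groups the model had.

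The section names two other analyses: multivariate regression of changes in beta cell function on clinical characteristics and on the adipoinsular and enteroinsular parameters, and a Mann-Whitney test against the BMI-matched non-bariatric controls. No contrast, pairwise test or two-group model for short- versus long-standing T2DM is written.

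**The concern.** A test of a three-level factor and a test of a two-group hypothesis have different nulls. The three-level Group by Time null holds only if short-standing T2DM, long-standing T2DM and non-diabetic patients all change alike. The primary null needs only the first two to agree. If diabetes duration has no effect and the non-diabetic patients simply follow another course, the primary null is true and the three-level null is false. The Group main effect has the same defect, because a constant difference in level between diabetic and non-diabetic patients is enough to reject it.

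The background makes such a difference plausible. It says that "Morbid obesity per se is associated with profound insulin resistance and subsequent hypersecretion of insulin", with the dynamics of beta cell function still intact, and contrasts this with a progressive loss of glucose sensitivity in overt diabetes.

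At stake is the study's central claim. A significant Group or interaction result could be reported as an effect of disease duration when it reflects only diabetic versus non-diabetic patients.

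**Working it through.** **1. The plan's own figures.** Attrition: 85 × (1 − 0.10) = 76.5 and 85 × (1 − 0.12) = 74.8, so the stated 75 completers are reproduced. The per-group requirements of 9, 13, 13 and 18 (α/power 0.05/0.80, 0.01/0.80, 0.05/0.95, 0.01/0.95) cannot be recomputed, because the AIR means, SDs and covariances behind them are not in the Protocol. Only their mutual consistency can be checked. Solving for the interaction noncentrality that needs 9 per group at α = 0.05 and power 0.80 gives a range that contains values reproducing all four figures. This works with two groups and also with three. The closing figure of 25 per group is equally ambiguous: 75/3 = 25 and 50/2 = 25.

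**2. Inputs for the mismatch.**
- From Methodology section 6: 50 T2DM completers, 40–50% of them long-standing (20–25 long, 25–30 short); 25 non-diabetic completers; three visits; α = 0.05.
- Assumed: short and long respond identically; the non-diabetic change from baseline differs by d at both follow-ups, with d in SDs of change; compound symmetry. Setting the SD of change to 1 gives within-patient residual variance σ² = 1/2, since Var(change) = 2σ².

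**3. Three-level Group by Time test.**
- df1 = (3 − 1)(3 − 1) = 4; df2 = (75 − 3)(3 − 1) = 144; 5% critical value 2.43.
- The extra non-diabetic profile is (0, d, d). Centred over time it is (−2d/3, d/3, d/3), with sum of squares 2d²/3.
- λ = [25 × 50/75] × (2d²/3)/σ² = 16.67 × 0.667d²/0.5 = 22.2d².
- Rejection probability = P(noncentral F(4, 144, λ) > 2.43).

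| d | λ | Three-level test rejects |
|---|---|---|
| 0 | 0 | 5.0% |
| 0.25 | 1.39 | 12.7% |
| 0.5 | 5.56 | 42.4% |
| 0.75 | 12.5 | 80.6% |
| 1.0 | 22.2 | 97.5% |

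The T2DM patients enter λ only through their total of 50, so 25/25/25 and 30/20/25 give the same results. Simulation (5,000 runs per cell) gave 43% at d = 0.5 and 97–98% at d = 1.0.

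**4. T2DM-only Group by Time test.** df1 = 2 and df2 = 2(50 − 2) = 96. With short = long, λ = 0 whatever the non-diabetic patients do. In the same simulations it rejected in 4.7–5.6% of trials.

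**5. Sensitivity to assumed AIR means.** Take 30/20/25 completers, within-patient correlation 0.5, CV 60–80%, non-diabetic AIR flat, and a small common T2DM rise from 100 to 120. The three-level test then rejects in roughly 9–19% of trials. The size depends strongly on the assumed courses. That the rate exceeds 5% whenever the non-diabetic change differs does not.

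**6. The opposite direction.** If long differs from short by 0.8 SD and non-diabetic patients lie midway, λ = 25 × 2 × (0.4)² × (2/3)/0.5 = 10.7 for both tests at 25 per group. Power is 0.73 for the three-level test (df 4, 144) and 0.83 for the two-group test (df 2, 96). The extra level can also cost power for the primary question.

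**The case against.** The strongest reply is that the Protocol never makes a significant omnibus F the rule for rejecting the primary null. Item 1 lists factors for many variables, and the interaction is mentioned only in the power text. A three-level model does not preclude a short-versus-long contrast, the third level serves the secondary objective on patients with and without T2DM, and contrasts are commonly left to a statistical analysis plan, which is not shown. This stands in part. One may not infer that the authors would declare a duration effect from the omnibus test. But the Protocol does fix a model whose Group tests address a different null from the stated one, so this is more than absent detail.

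Four stronger readings are tempting and lack support:
- *The ANOVA is the only route to the duration question.* The planned regression on clinical characteristics could include diabetes duration, which is recorded and verified at baseline, although duration is not named there.
- *The background predicts different courses.* The obesity statement describes a state, not a course after surgery. The AIR restoration that is cited comes from biliopancreatic diversion, and the Protocol says recovery after gastric bypass is still unclear. A different course is plausible, not predicted.
- *The sample size was computed for three groups.* The figures fit two groups equally well.
- *Larger AIR variance in non-diabetic patients inflates the pooled error and hides a real short-versus-long difference.* No AIR variance appears in the Protocol, and section 6 prescribes log transformation for non-Gaussian data, which would largely remove such a difference.

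**Conclusion.** The point holds as a mismatch between hypothesis and stated model. The primary null compares two groups of diabetic patients; the Group and Group by Time tests of the written ANOVA concern three groups and can reject when the primary null is true. Under the assumed differences of 0.25 to 1.0 SD in non-diabetic change, that happens in about 13% to 97.5% of trials, against about 5% for a T2DM-only test. These magnitudes are illustrative, because no AIR values are given and compound symmetry is assumed; with a small T2DM rise the rate may be only 9–19%. The direction does not depend on the values chosen: the three-level interaction test keeps its 5% level for the primary null only if non-diabetic patients change exactly as diabetic patients do. The risk materialises only if the omnibus result is read as the answer to the primary question, which the Protocol neither states nor rules out.

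**What to change.** In Methodology section 6, item 1, name the short- versus long-standing T2DM by Time comparison of AIR as the primary test. Fit it in T2DM patients only, or as a named contrast within the three-group model. Keep the three-group comparison with non-diabetic bariatric patients as secondary. In the power paragraph, state how many groups and which comparison the 9, 13, 13 and 18 per-group figures cover; if they were not computed for short versus long, recompute them for that comparison.

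The cost is a few sentences in the Protocol, plus one recalculation at most. Patients, visits and data collection do not change.

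### The ANOVA for the short- versus long-standing T2DM comparison takes about a third of its error variance from non-diabetic patients, and nothing protects the test if their spread differs

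*Protocol*

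**What the plan says.** The primary objective is "Comparison of the changes in beta cell function following gastric bypass in patients with short- and long-term history of T2DM", with AIR during the IVGTT as the primary variable.

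Section 6 (Statistical analysis), item 1, names the method: "Changes in beta cell function and other variables after gastric bypass surgery will be assessed by analysis of variance (ANOVA) with repeated measures". The between-subject factor is a "comparison between groups of bariatric patients with short- and long-standing T2DM and bariatric patients without T2DM", so it has three levels. Time is the within-subject factor, with three occasions. The only stated distributional safeguard is: "In case of non-Gaussian distribution, log transformed data will be assured for further statistical evaluation".

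The power paragraph of the same section uses a model with subject, group and time. It says that the sponsor "estimated mean values, variation and time-dependent covariance in individual groups for AIR (pmol/l") from a published study, but prints none of these values. Expected completers are 50 with T2DM, of whom 40-50% are long-standing, and 25 without diabetes.

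The Background section says that morbid obesity leads to "subsequent hypersecretion of insulin but the dynamics of beta cell function are still preserved", whereas "overt diabetes is characterized by a progressive loss of beta cell glucose sensitivity". It also reports that AIR was restored in T2DM after biliopancreatic diversion, and leaves open whether this happens after gastric bypass.

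**The concern.** A classical repeated-measures ANOVA estimates one error variance and applies it to every contrast among the groups. The primary contrast involves two of the three groups, yet its standard error also depends on how variable the third group is. If non-diabetic patients vary more in their change in AIR than T2DM patients do, the standard error is too large and power is lost. If they vary less, it is too small and the test rejects too often.

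The protocol's description gives reason to doubt equal spread. One group starts with preserved dynamics and high secretion. The others start with an impaired response that may recover quickly, slowly or not at all, over a deliberately wide range of disease duration. The log rule need not remove such a difference, because it is triggered by the shape of the distribution and not by unequal variances.

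**Working it through.** **The plan's own figures.** The power paragraph gives 9, 13, 13 and 18 subjects per group for (α, power) = (0.05, 0.80), (0.01, 0.80), (0.05, 0.95) and (0.01, 0.95). They cannot be reproduced from inputs, since no mean, SD or covariance is printed. They are consistent with one another: a noncentral F calculation with noncentrality proportional to n returns exactly 9/13/13/18 for a three-group between-subject test (2 numerator df), and also for a two-group test (1 numerator df), each with a suitable effect size. They therefore reveal nothing about the group SDs.

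**Share of the error from non-diabetic patients.** With 40% long-standing T2DM there are 30 short-standing, 20 long-standing and 25 non-diabetic completers. For one change score per patient the error df are 29 + 19 + 24 = 72, and 24/72 = 1/3. With 25/25/25 the share is the same. For the group-by-time error over three visits the df double to 48 of 144, again one third.

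**Effect on the standard error.** Let k be the SD of change in non-diabetic patients divided by that in T2DM patients, taken as equal in the two T2DM groups. The protocol does not give k, so the range below is an assumption.

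Pooled SE / true SE = √[(29 + 19 + 24k²)/72] = √[(2 + k²)/3]

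True two-sided type I error at nominal 5% ≈ 2[1 − Φ(1.96 × ratio)]

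For example, k = 0.5 gives √(2.25/3) = 0.87, and k = 2 gives √(6/3) = 1.41.

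| k (assumed) | SE ratio | Type I error, formula | Type I error, simulated |
|---|---|---|---|
| 0.5 | 0.87 | 9.0% | 8.6-9.0% |
| 0.8 | 0.94 | 6.6% | 6.5-6.6% |
| 1 | 1.00 | 5.0% | 4.9-5.0% |
| 1.5 | 1.19 | 2.0% | 2% |
| 2 | 1.41 | 0.6% | 0.6-0.7% |

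The simulations used normal change scores and 30/20/25 patients, with 40,000 trials per setting in the main runs. Ranges are across repeat runs.

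**Power.** Take a true difference of 0.82 T2DM SDs, which gives about 80% power when only T2DM variance is used. The pooled-error test then has about 80% power at k = 1, 68-69% at k = 1.5 and 51-52% at k = 2. A Welch contrast of the two T2DM groups has about 79% power throughout, with type I error of about 5%.

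**Level alone does no harm.** With equal SDs, shifting the non-diabetic mean by 0, 5 or 50 SDs left the type I error at 4.9%, 5.0% and 4.8%. Only unequal spread matters.

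**The case against.** A reader might infer that the standard error of the primary comparison is simply wrong because, by the protocol's own account, AIR differs greatly between diabetic and non-diabetic patients. The documents do not support that. The Background statements are qualitative and concern the level of beta cell function. A difference in level is absorbed by the group factor, as the last check shows. No AIR mean, SD or variance ratio is printed.

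Nor can a direction be asserted. Hypersecretion might widen the non-diabetic spread. A mixture of patients who do and do not recover might instead widen the spread of change in T2DM. If SD rises in proportion to the mean, the log transformation brings k back to about 1. A claim that the log scale reverses the error has no basis in the text.

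A larger figure is also tempting. If the long-standing group had twice the SD of the short-standing group and k were 0.7, the pooled test would run at about 14%. Much of that has nothing to do with non-diabetic patients: pooling the two T2DM groups alone already gives about 8.3-8.6%.

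Estimating variation by group for a power calculation does not commit the analysis to group-specific variances, so the power paragraph and item 1 do not contradict each other.

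Finally, covariance structure and degrees of freedom are commonly settled in an analysis plan, which is not at hand and may already deal with this. What remains is that the protocol itself names the model and puts the third group into it. The usual reading of that model is a common error variance, and the only check stated is for normality.

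**Conclusion.** The point stands as a conditional weakness in a stated method. In the classical form of the named ANOVA, one third of the error variance for the primary contrast comes from patients who take no part in it. Equal spread is doubtful on the protocol's description but is not contradicted by any figure in it.

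Over the assumed range of k from 0.5 to 2, the true type I error runs from about 9% to below 1%, and power at k = 2 falls from about 80% to just over 50%. At k = 1 there is no error, and for k near 1 it is small. These figures rest on normal change scores, 30/20/25 completers and equal SDs within T2DM. The true ratio is not known.

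Borrowing error from the non-diabetic group gains almost nothing when variances are equal, so the protection is worth having. This is a cheap improvement, not the correction of a demonstrated mistake.

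**What to change.** In section 6, item 1, add a sentence on the primary contrast. It should state that the short- versus long-standing T2DM comparison of change in AIR takes its error from the two T2DM groups only, without assuming equal variances (Welch). Alternatively, it should come from a repeated-measures model with a separate covariance matrix per group and Satterthwaite or Kenward-Roger degrees of freedom. Restricting the pooling to T2DM patients is not enough by itself, because the two T2DM groups may differ in spread and in size.

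Fix this in advance and do not make it depend on a variance test in the data, which would leave the choice of error term open until results are seen. If the analysis plan already specifies such a contrast, a cross-reference is sufficient.

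The cost is one sentence and one model option. If the variances are in fact equal, power falls by about 1 percentage point, from about 80% to about 79%.
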